#### Analysis of smartwatch data

Raw indoor and outdoor temperature and relative humidity data, collected in 15-min intervals, will be averaged at the hourly level. We will categorize environmental data as anomalies when measurements are two standard deviations beyond the corresponding monthly average values based on roof type (mud brick or tin roof).

We will analyze data from smartwatches on heart rate and sleep. First, for heart rate data, we will exclude duplicate heart rate measurements or those that exceed the age-predicted maximum heart rate as implausible values. We will round and aggregate remaining heart rate measurements to the nearest 1-h interval to align with summarized indoor and outdoor temperature and relative humidity data. To distinguish daytime and nighttime heart rates, we will use median sleep onset and offset to define nighttime from 22:00 to 06:00 h. Measurements will be analyzed if they reach the threshold of at least 1 h during the same day or night, with a minimum of one measurement every 15 min. The 15-min threshold was selected based on previous research [53]. Second, for sleep data, we will calculate sleep duration based on onset and offset time to eliminate errors and minimize outliers. Only overnight sleep periods, where nighttime sleep is defined as having a sleep onset of ≥ 17:00 and a sleep offset of ≤ 13:00, with a 2-h adjustment made to account for earlier bedtimes of the study population, will be included in the analysis. If a participant has multiple sleep observations in a single night, we will aggregate these into one sleep observation by adding the sleep duration values and the duration between the first offset and last onset to the wake time after sleep onset. We will exclude data where multiple sleep observations overlap for a participant. Furthermore, sleep detections with a time difference of fewer than 3 h between sleep onset and sleep offset will be excluded, in line with the manufacturer’s declaration that such detections represent invalid measurements.

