We will evaluate the intervention effects of temperature exposure on heart rate and sleep outcomes using generalized additive mixed models, with individuals nested within households as random terms. Natural cubic splines will be used to evaluate non-linear effects. In cases where non-linear effects are not detected, linear terms will be substituted in the final models. We will present effect estimates of daily exposure averages on daytime versus overnight periods when individuals are most likely present in their homes. Furthermore, we will present intervention effects during the hottest month (April), monthly aggregates, and an overall aggregate for the entire study period. Where relevant, models with continuous daily or intraday time series data will include the day of the year and month indicators to account for time trends and seasonality, respectively. We will present supplementary models with an interaction term between the intervention group and roof type to assess variations resulting from the thermal characteristics of household vernacular architecture.

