## Methods: monitoring

We have appointed an independent steering committee comprising three members: a climate change and health domain expert, a clinical trials expert, and a biostatistician to maintain project oversight throughout the study. The steering committee will convene three meetings, the last of which will be in June 2023. At these meetings, the research team will review the conduct of the trial, including a review of adherence to intervention components, logistical issues, and completeness and quality of collected data. Our biostatisticians will also present emerging effect estimates in the intervention and control arms to the steering committee, who will ascertain whether the results display:Null finding(s) > indicating the study should stopSignificant finding(s) > indicating the study should stopEmerging positive finding(s), but statistically insignificant > indicating the study should potentially continue, and therefore, the data collection should continue for a recommended duration.

The cool roof is a passive home cooling intervention and, therefore, required no human interaction or behavior change on behalf of our participants. We conducted an education program through our field staff to ensure study participants did not place items on their roofs that could obstruct the optimal performance of the cool roof. Our field teams regularly monitored roofs during monthly home visits and highlighted any deterioration or other issues for resolution. Throughout the trial, our study team exchanged regular communication via virtual and phone calls, emails, and short messages about trial progress.

We encountered, however, adherence issues with participants removing smartwatches, particularly at night. Our field team explained the importance of smartwatch data and encouraged non-compliant individuals to wear the device during home visits.

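### In the 152-person smartwatch subset, 1 h of data is enough for a night to count and no clock-hour term is named, so the overnight heart-rate estimate mixes short fragments with full nights

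*Protocol article*

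**What the plan says.** The rule is in the protocol article under Analysis of smartwatch data. Night is fixed by this sentence: "we will use median sleep onset and offset to define nighttime from 22:00 to 06:00 h". Inclusion is then set by "Measurements will be analyzed if they reach the threshold of at least 1 h during the same day or night". Within that time, readings may be no sparser than one per quarter of an hour. The only justification given concerns this spacing: "The 15-min threshold was selected based on previous research". No reason is given for the 1 h minimum. Heart-rate readings are first reduced to hourly values so that they line up with the hourly temperature data.

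The same section says that effects will be presented for "daytime versus overnight periods when individuals are most likely present in their homes". On time adjustment, it says that models with daily or intraday series, where relevant, "will include the day of the year and month indicators to account for time trends and seasonality, respectively". It states no minimum share of the night, no weighting by coverage and no term for hour of the clock.

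Methods: monitoring reports "adherence issues with participants removing smartwatches, particularly at night" and says that field staff encouraged people to keep wearing them. It gives no rate, no removal time and no split by arm. The Outcomes section puts the watch subset at 152 participants, 76 per arm. Methods: assignment of intervention says that households know their allocation.

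**The concern.** The inclusion minimum is lowest in relation to need in the period where wear is known to be poor, and that is also the period in which the article expects people to be at home under the roof being tested. A night with four readings and a night with 32 or more both qualify.

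If heart rate changes over the night, a fragment and a full night estimate different quantities. Day of year and month describe the calendar, so they cannot separate a change in heart rate from a change in the hours recorded.

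Two consequences follow, and they need to be kept apart. The first comes from the rule itself: extra variability, and an overnight value whose meaning varies from night to night. The second is conditional. Wear happens after randomisation and households are unblinded, so coverage could differ between arms. If it did, part of any heart-rate difference would reflect the hours observed and not an effect on heart rate.

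**Working it through.** The article gives no figure that depends on this rule, so there is nothing to reproduce. The check is coverage arithmetic followed by an illustration.

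**Inputs from the article:** night 22:00 to 06:00; minimum 1 h; one reading per 15 min; hourly aggregation; time terms day of year and month.

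**Inputs assumed, because the article does not give them:** the heart-rate profile over the night, the share of accepted nights that hold only the first hour, and how that share differs by arm.

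**Coverage.** 1 h / 8 h = 12.5%. At one reading per 15 min, that is 4 readings against 8 × 4 = 32 for a full night.

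**Gap between a fragment and a full night.** Assume 75 bpm in the first hour and 63 bpm in the other seven.
- Full-night mean: (75 + 7 × 63) / 8 = 516 / 8 = 64.5 bpm.
- First-hour-only night: 75 bpm, a gap of 10.5 bpm.

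**Artefact with no true effect.** Let p be the share of accepted nights that hold only the first hour: 20% in control, 15% in intervention.
- *Each night weighted equally:* difference = (0.20 − 0.15) × 10.5 = 0.525 bpm.
- *Hourly rows pooled* (a fragment is 1 row, a full night 8): mean = [75p + 516(1 − p)] / [p + 8(1 − p)].
  - Control: (15 + 412.8) / (0.2 + 6.4) = 427.8 / 6.6 = 64.82.
  - Intervention: (11.25 + 438.6) / (0.15 + 6.8) = 449.85 / 6.95 = 64.73.
  - Difference: about 0.09 bpm, roughly one sixth of the equal-weight figure.

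**Range over the imbalance** (control at 20%):

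| First-hour-only nights, control vs intervention | Equal weight per night | Hourly rows pooled |
|---|---|---|
| 20% vs 20% | 0 | 0 |
| 20% vs 18% | 0.21 bpm | 0.04 bpm |
| 20% vs 15% | 0.53 bpm | 0.09 bpm |
| 20% vs 10% | 1.05 bpm | 0.17 bpm |

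**Range over the profile.** The 12 bpm step after the first hour is steep. Suppose instead a linear fall of D bpm over the 8 h. The first hour then exceeds the full-night mean by D × 7/16, which is 1.75 bpm for D = 4 and 4.4 bpm for D = 10. With fragment shares of 40% versus 30%, the artefact is 0.18 to 0.44 bpm with equal weight per night and 0.05 to 0.11 bpm with rows pooled. With a flat profile it is zero.

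**Which unit applies.** The article supports either. It builds hourly heart-rate values, but it also speaks of effects of daily exposure averages for day and night.

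**Check of the remedy.** In the illustration the arms have the same mean within every clock hour (75 against 75, then 63 against 63). A model that compares arms within clock hour therefore returns zero. A higher minimum alone does not: under the linear fall, with 40% versus 30% and equal weight per night, fragments of 4 h in place of 1 h still leave 0.10 to 0.25 bpm.

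**The case against.** A reader might infer that the overnight comparison is biased in favour of the cool roof. The article does not support that. It reports no difference in wear between arms, and with equal wear the arm bias is zero. The direction in the illustration comes from the assumption that control homes have more fragments. This part of the objection stands in full.

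A reader might also infer that the fragments are early-night, waking values. That is not documented either. Removal times are not given. The 22:00 boundary is the median sleep onset, so about half of onsets fall at or before it and the first hour is not plainly a waking hour. A watch taken off at or before about 22:00 yields less than 1 h, and that night drops out. That is a selection problem and not a mixing problem. The 12 bpm step is therefore an assumption and no more.

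The larger figures also need each night to carry equal weight. If hourly rows are modelled, fragments carry little weight, as shown above.

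The scope is limited. The monthly home-visit readings that supply the primary intention-to-treat analysis are untouched, although Table 2 also names the watch as a measurement of the primary endpoint in a subset. The 3 h minimum for sleep detections is a manufacturer's validity rule and does not show that 1 h is wrong for heart rate.

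Finally, the named time terms are not said to be exhaustive, and a condensed article may leave further terms to an analysis plan that is not shown. This has force for wear-time tables and sensitivity analyses. It has less force for the inclusion rule: the article states the 1 h minimum outright and names time terms that cannot compensate for it.

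**Conclusion.** The point holds in a limited form. As written, the rule lets 12.5% of a night stand for the night in a subset where night-time removal is already known, and none of the named model terms accounts for the hours recorded. Mixing and a less clearly defined overnight estimate follow from the rule as soon as partial nights occur. Bias between arms is a possibility only, and it depends on differential wear that the article does not report.

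Under the assumed 75/63 bpm profile and shares of 20% versus 15%, the artefact is about 0.09 bpm with pooled rows and about 0.5 bpm with equal weight per night. A mixed model could fall between the two. The profile, the shares and the imbalance are all assumptions, so these figures show scale and are not estimates for this trial. The change is worth making because it is cheap and because, without wear hours by arm, nobody can tell which case applies.

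**What to change.** - In the day and night watch heart-rate models, use the hourly values already planned and add a clock-hour term (a factor or a cyclic spline). Alternatively, form each night value as an hour-standardised mean over 22:00 to 06:00. State which unit is modelled.
- Report hours worn by arm and by clock hour, including nights excluded for having less than 1 h.
- Repeat the overnight analysis with a stricter coverage minimum, for example at least 4 h. Keep this as a sensitivity analysis only, because it selects on behaviour after randomisation.

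The cost is analysis code and one table, with no new data. The stricter-coverage analysis uses fewer nights, so its intervals will be slightly wider. The clock-hour term handles which hours were recorded. It does not correct for which people or nights have any data at all, and for that the wear table is the safeguard.

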**Secondary endpoints**	
**Air temperature**	Definition: Ambient air temperature (in °C) Functional form: Continuous Measurement: DS1923 iButton Hygrochron heat and humidity measurement device
**Relative humidity**	Definition: Ratio of the amount of water vapor present in the air to the greatest amount possible at the same temperature (in %) Functional form: Continuous Measurement: DS1923 iButton Hygrochron heat and humidity measurement device
**Heat index**	Definition: Index that combines air temperature and relative humidity (using the formulae endorsed by the US National Oceanic and Atmospheric Administration (NOAA)) Functional form: Continuous Measurement: DS1923 iButton Hygrochron heat and humidity measurement device
**Indoor thermal comfort**	Definition: Current heat experience measured using heat strain score index. A score of < 13.5 indicates no or low heat strain, between 13.6–18 indicates potential for heat-induced illness, and > 18 indicates the onset of heat-induced illness Functional form: Categorical Measurement: Heat strain score index scale comprising 18 questions answered by individuals at the time of interview
**Systolic blood pressure**	Definition: Systolic blood pressure in mmHg Functional form: Continuous Measurement: Omron portable automated sphygmomanometers
**Diastolic blood pressure**	Definition: Diastolic blood pressure in mmHg Functional form: Continuous Measurement: Omron portable automated sphygmomanometers
**Body temperature**	Definition: Body temperature Functional form: Continuous Measurement: Inner ear thermometer
**Dehydration**	Definition: Loss of fluid greater than intake amount resulting in the body being unable to carry out its normal functions Functional form: Categorical Measurement: Urine hydration chart and question answered by individual
**Blood glucose (HbA1c)**	Definition: Average blood glucose measured over 3 months Functional form: Continuous Measurement: HemoCue® HbA1c 501 System to capture estimated average glucose (g/L)
**Sleep**	Definition: Number of hours slept and number of times the individual woke up Functional form: Count Measurement: Recall question answered by individual and smartwatch (in a subset of the cRCT population)
**Cognition**	Definition: The mental processes involved in gaining knowledge and comprehension Functional form: Continuous Measurement: Oxford Cognitive Screen (OCS)-Plus (assessing memory, language, visual-spatial ability, and executive functioning domains)

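### Read plainly, watch sleep duration counts a waking as sleep when the night is one detection but not when the watch splits it, so it does not match hours slept

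*Protocol article*

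**What the plan says.** Table 2 of the protocol article defines the secondary endpoint sleep as "Number of hours slept and number of times the individual woke up". It is measured by recall in all participants and by smartwatch in a subset. The Outcomes section puts that subset at 152 participants, 76 per arm, and reports that the watch model was replaced in July 2022.

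The section on analysis of smartwatch data gives the derivation:

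- For duration: "we will calculate sleep duration based on onset and offset time to eliminate errors and minimize outliers".
- For a night with more than one detection: "we will aggregate these into one sleep observation by adding the sleep duration values". The time between detections goes elsewhere, because the rule also adds "the duration between the first offset and last onset to the wake time after sleep onset".
- For short detections: "sleep detections with a time difference of fewer than 3 h between sleep onset and sleep offset will be excluded".

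No sentence says that wake time recorded inside a detection is taken off its duration.

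**The concern.** Onset and offset alone give the length of the sleep period. They do not give the time spent asleep within it. The rule for several detections shows that the plan treats wake after sleep onset as a quantity of its own and does not count a gap between detections as sleep. A waking is therefore handled in two ways. Inside one detection it stays in the duration; between two detections it is removed. Which of these applies is decided by the watch, not by how the person slept.

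Night waking is a plausible route by which indoor heat shortens sleep. If a cool roof reduces waking while bedtime and rising time stay the same, unsplit nights show no gain in watch-measured hours slept. The same section plans April effects and an aggregate over the whole study period. April 2022 fell in the period of the first watch model and April 2023 in that of the second, so the pooled estimate relies on duration meaning the same thing under both.

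**Working it through.** The article states no sample size, power or expected effect for watch sleep duration, so there is no figure of its own to reproduce. The check applies the stated rules to example nights.

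**Inputs**

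- Duration rule, rule for several detections and 3 h minimum: analysis of smartwatch data.
- Night window 22:00 to 06:00: same section, "we will use median sleep onset and offset to define nighttime from 22:00 to 06:00 h".
- Time awake during the night, w: not given. Assumed range 0.25 to 2 h.
- Share of waking time that falls between detections, s: not given. Possible range 0 to 1.

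**Step 1: one night, two records.** Asleep at 22:00, awake 01:00 to 01:45, up at 05:00.

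- Time asleep: 7.0 − 0.75 = 6.25 h.
- One detection: 05:00 − 22:00 = 7.0 h.
- Two detections (22:00 to 01:00 and 01:45 to 05:00): 3.0 + 3.25 = 6.25 h, with 0.75 h going to wake after sleep onset.

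Neither part is shorter than 3 h, so the exclusion rule plays no role here.

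**Step 2: the 8 h window, before any exclusion.** Unsplit duration = offset − onset = 8.0 h whatever w is. Split duration = 8.0 − w.

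| w (h, assumed) | Unsplit (h) | Split (h) | Difference (h) |
|---|---|---|---|
| 0.25 | 8.0 | 7.75 | 0.25 |
| 0.5 | 8.0 | 7.5 | 0.5 |
| 1 | 8.0 | 7.0 | 1.0 |
| 1.5 | 8.0 | 6.5 | 1.5 |
| 2 | 8.0 | 6.0 | 2.0 |

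The same night differs by exactly the time awake.

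**Step 3: effect on the comparison of arms.** Let the arms have equal onset and offset times, the same s, and mean waking times W(control) and W(cool roof).

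- True difference in sleep = W(control) − W(cool roof).
- Measured difference = s × true difference.
- Attenuation = 1 − s.

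For illustration only, assume 60 and 45 min awake, a true difference of 15 min:

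- s = 0: 0 min measured, attenuation 100%.
- s = 0.5: 7.5 min measured, attenuation 50%.
- s = 1: 15 min measured, attenuation 0%.

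The article gives nothing that narrows s, so the range is 0 to 100%. It applies only to benefit that acts through wakings; an earlier onset or later offset is captured in full.

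**Step 4: the night of Step 1 with recorded wake subtracted.**

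- Unsplit: 7.0 − 0.75 = 6.25 h.
- Split: (3.0 − 0) + (3.25 − 0) = 6.25 h.
- Span from first onset to last offset: 7.0 h in both.

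Both measures now agree across the two records, provided the watch registers the 45 minutes as wake.

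**The case against.** The text says that duration is based on onset and offset; it does not spell out a subtraction. Wake inside a detection might be netted off in a fuller document that is not shown. That possibility stands, and it is why the point rests on a plain reading. The reading is nevertheless the natural one. Only two times are named, the 3 h rule in the same section uses the difference between them, and the article otherwise sets out this algorithm in detail.

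The authors also give a reason for their choice, namely to limit errors and outliers. That reason has weight. Subtracting watch-detected wake makes the result depend on wake detection by two different models, so the remedy has a device dependence of its own.

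A reader might infer that the trial cannot detect an effect on night waking. The documents do not support that. The same endpoint includes the number of awakenings, sleep is also measured by recall, and wake after sleep onset is kept as a variable. None of these makes the watch duration consistent, but each leaves another way to see such an effect.

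A reader might also infer that the change of watch biases the comparison of arms. Nothing in the article shows that the two models split nights differently, and the replacement is described without any distinction between arms. A shift in what duration measures over time is possible but not demonstrated.

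**Conclusion.** The point holds as an inconsistency in one derived variable. On the plain reading, the watch duration is a sleep period on unsplit nights and a sleep period less the gaps on split nights. Neither is generally the hours slept that Table 2 names, since wake inside a detection also stays in the duration on split nights.

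For a given night the discrepancy equals the waking time that does or does not split the detection: 0.75 h in the worked night. For a treatment effect acting through wakings, attenuation toward zero lies between 0 and 100%. That rests on equal onset and offset times and the same split share in both arms. A reader might infer a heavy loss, of half or more, but that would require knowing that at most half of waking time falls between detections, and the article gives no such figure.

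The scope is narrow: one secondary endpoint in 152 of 1200 participants. The primary endpoint, recalled sleep and the awakenings count are untouched. The change is worth making because the rule as stated gives two values for one night and the correction is cheap.

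**What to change.** State two watch measures, each computed in the same way for split and unsplit nights:

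1. Hours slept: for each detection, offset minus onset minus the wake recorded within it, summed over that night's detections.
2. Sleep period: last offset minus first onset.

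Present both, and check that the result holds within each device period, before and after the July 2022 change. The second measure keeps the authors' reliance on onset and offset and does not depend on the watch's wake detection, so it guards against the weakness of the first. If subtraction of wake within detections was already intended, one clause saying so settles the first measure.

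Full agreement between split and unsplit nights also requires that no part of a split night is lost to the 3 h exclusion. The article does not say whether that rule comes before or after merging, so the order should be stated.

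The cost is a few lines of wording and code. No new data should be needed, since the merging rule already uses a wake-after-onset variable. The price is that hours slept then relies on wake detection by two watch models, which is why both measures and the check by device period belong together.

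### Smartwatch sleep is computed from recorded onset and offset with no check that the watch was worn, although removal at night is reported

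*Protocol article*

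**What the plan says.** The Protocol article, under Analysis of smartwatch data, sets out the sleep processing in some detail. Duration comes from the recorded times: "we will calculate sleep duration based on onset and offset time to eliminate errors and minimize outliers". The filters that follow are:

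- an overnight window, with onset from 17:00 and offset by 13:00;
- merging of several detections in one night, with durations summed and "the duration between the first offset and last onset to the wake time after sleep onset" added as wake time;
- overlap: "We will exclude data where multiple sleep observations overlap for a participant";
- a minimum length: "sleep detections with a time difference of fewer than 3 h between sleep onset and sleep offset will be excluded", attributed to the manufacturer.

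The same section gives heart rate a coverage rule: at least 1 h in the same day or night, "with a minimum of one measurement every" 15 min. That rule sits under the heart-rate step; the sleep step has no counterpart.

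Methods: monitoring reports: "We encountered, however, adherence issues with participants removing smartwatches, particularly at night". The response described is explanation and encouragement by field staff at home visits. No analysis rule follows from it.

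Table 2 lists sleep as a secondary endpoint, measured by recall and, in a subset, by smartwatch. The Outcomes section gives that subset as 152 participants, 76 per arm, and reports a change of watch model in July 2022.

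**The concern.** Each sleep filter tests clock time, overlap or length; none tests wear. Someone asleep from 22:00 whose watch comes off at 02:00 could be entered with 4 h of sleep, which passes every filter. If the watch comes off before 3 h, the night is dropped. If it is taken off, put back on and sleep is detected again, the off-wrist interval is booked as wake time. Adherence behaviour can thus become an outcome value.

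Two results are exposed. One is the level of watch-measured sleep, which would be too low in any arm where such removals occur. The other is any contrast across which removal varies: between arms, or along the temperature axis, since the plan models temperature exposure against sleep and reports April, monthly and overall effects. The change of watch model could also shift how non-wear is handled partway through follow-up.

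**Working it through.** The plan states no removal rate and no figure for this point, so there is nothing to reproduce. What follows is an illustration.

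**Inputs from the Protocol article.** Night window 22:00 to 06:00, that is 8 h; minimum span 3 h; 152 watch wearers among 1200 participants (152/1200 = 12.7%).

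**Assumptions, not in the documents.** True sleep is 8 h every night. The watch is removed on a share q of nights, at a time uniform over the 8 h. The device records removal as sleep offset, and the watch is not put back on.

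**Step 1: what the 3-h filter catches.** Removal before 3 h has probability 3/8 = 37.5%, and those nights are dropped. The other 5/8 = 62.5% are kept. Their mean recorded sleep is (3 + 8)/2 = 5.5 h, a loss of 2.5 h = 150 min per night.

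**Step 2: mean understatement among retained nights.**

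L(q) = 150 × 0.625q / [(1 − q) + 0.625q] = 150 × 0.625q / (1 − 0.375q)

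- q = 20%: 150 × 0.125/0.925 = 20.3 min
- q = 30%: 150 × 0.1875/0.8875 = 31.7 min

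| q | Falsely short share of retained nights | Understatement (min) |
|---|---|---|
| 5% | 3.2% | 4.8 |
| 10% | 6.5% | 9.7 |
| 20% | 13.5% | 20.3 |
| 30% | 21.1% | 31.7 |
| 40% | 29.4% | 44.1 |
| 50% | 38.5% | 57.7 |

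**Step 3: arm contrast.** The spurious difference, cool roof minus control, is L(q control) − L(q cool roof).

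| Control | Cool roof | Spurious difference (min) |
|---|---|---|
| 20% | 20% | 0 |
| 30% | 20% | 31.7 − 20.3 = +11.4 |
| 20% | 30% | −11.4 |
| 20% | 10% | +10.5 |
| 10% | 20% | −10.5 |
| 40% | 20% | +23.8 |

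The same arithmetic applies with hotter and cooler nights in place of the arms, so the temperature–sleep relation can be biased even when removal is balanced by arm.

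**Step 4: the merging rule.** Suppose a participant sleeps from 22:00 to 06:00 apart from moments spent handling the watch, which is off from 01:00 to 03:00. Both detections last 3 h and are kept. Recorded sleep is 3 + 3 = 6 h, and the 2-h gap enters wake time after sleep onset.

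**Step 5: would the heart-rate coverage rule suffice if extended to sleep?** No. A watch worn from 22:00 to 02:00 has 4 h of readings and meets the 1-h threshold, yet the night is still entered as 4 h of sleep. The informative readings are those after the recorded offset and across the gap.

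**The case against.** The strongest case against has four parts.

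**The mechanism is inferred.** Nothing says how either watch model records removal: as an offset, a void night or an off-wrist flag. The 3-h rule shows that the manufacturer already declares some detections invalid, and there may be other such rules. This stands; the point is conditional on it.

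**Removal may happen before bed.** The reported behaviour fits that reading too, and it would produce a missing night, not a short one. A person who removes the watch at 02:00 is also awake at that moment, so the offset is partly real; only later sleep is lost. This stands as well. The uniform removal time is a convenience with no support in the text.

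**A condensed article may leave wear rules to another document.** This carries less weight here. The section fixes the sleep algorithm step by step and sets a coverage rule for heart rate, then omits one for the endpoint most exposed to night-time removal. Followed as written, the rules can count off-wrist time as wakefulness.

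**Reach is small.** The watch covers 152 of 1200 participants for one secondary endpoint that also has a recall measure. The steering committee also reviews data completeness and quality. That limits the consequence but does not supply a rule.

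A reader might infer more: that heat makes people take the watch off, so control homes gather more falsely short nights and the cool roof is credited with a spurious sleep benefit. The documents do not support this. Methods: monitoring gives no cause, rate, time of night, month or arm for the removals. Equal removal gives no arm bias, and more removal in cool-roof homes gives bias against the intervention.

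**Conclusion.** The point holds in conditional form. The sleep rules have no wear condition although night-time removal is a reported problem, and the stated aim of eliminating errors is not met for this error. If removal is logged as offset, sleep is understated wherever removals after 3 h occur: about 20 min at 20% of nights and 32 min at 30%, given 8 h of true sleep and uniform removal times. Bias in the arm contrast or the temperature–sleep relation arises only if removal varies by arm or temperature, and its sign is open: 0 if equal, +11 or −11 min at 30% versus 20%. These sizes show sensitivity to assumed rates; they do not estimate an error in this trial. Neither the primary endpoint nor recalled sleep is touched by these sleep rules. The repair is worth making because it is cheap and would show whether the problem is real.

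**What to change.** Add a wear check to the sleep processing, using the watch's own heart-rate stream:

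1. Require heart-rate readings through the recorded sleep span, across any merged gap, and shortly after the recorded offset (for example over the next 30 to 60 min). The 15-min spacing already set for heart rate can serve.
2. Treat nights that fail as censored or missing, not as short sleep, and do not count an uncovered gap as wake time.
3. Report the share of failing nights by arm, month and night temperature. Given the change of device, a split by watch model is also useful.
4. Present the sleep results with and without the check.

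The cost is a processing rule on data already held. It assumes that heart-rate readings stop when the watch is off the wrist, which should be confirmed for both models. Some valid nights will be lost when the watch is removed right after true waking. Limiting the post-offset check to early offsets, say before about 04:00, would keep most of these, but it would still lose genuine early wakers and would let later removals through. Exclusion or censoring may itself be related to sleep, so the checked analysis is not free of bias either. That is why both versions should be reported. If failing nights prove rare and balanced, the sleep result is strengthened.
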